## Methods: participants, multi-level intervention, and outcomes

### Study design

This study uses a Type 1 hybrid implementation design with a non-randomized approach (30) (see **Figure 1**). While the primary focus of our study is to test the intervention, we are also very interested in understanding implementation related factors. As a result, we are collecting process data along every step of **Figure 1**, including for example, the number of referrals and patients screened, number of patients determined eligible and reasons for ineligibility, number of patients who agree to treatment and attend at least one appointment.

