### Study site

The study site is a safety-net hospital located in Sandoval County, NM. Sandoval County is the 4^th^ most populous county in NM, with 131,561 residents and covering 3,716 square miles. 40% of the residents are Hispanic and 14.1% are Native American (NA). Most health care services in Sandoval County are available in the “metro” corner, which is only 150 square miles and where two-thirds of the county’s population reside. The “nonmetro” area is home to 13 sovereign tribal nations, including 10 Pueblos, two Navajo chapter houses and a portion of the Jicarilla Apache reservation. This is the second highest number of reservations of any county in the U.S. The nonmetro area covers over 3,500 square miles and residents struggle with limited access to healthcare and high rates of poverty, mental health problems, substance use and suicide. In Sandoval County, the alcohol related death rate for NA is 174.2 per 100,000 compared to 56.0 and 35.1 per 100,000 for the overall state and U.S., respectively (31). Sandoval County is one of the top five counties with the highest number of methamphetamine-involved overdose deaths and has the 2nd highest number of opioid overdose related ED visits in the state (N=363, 6.1%) (31). The study period is October 2022 – September 2024. This study has been registered on the ISRCTN registry # ISRCTN33100750.

The study site hospital houses 72 inpatient beds, divided between two medical surgical units and one intensive care unit. The ED has 20 licensed beds. Fiscal year 2021 data from the study site hospital showed that 1,366 patients, representing 1,958 visits, accessed the ED with a SUD diagnosis (including alcohol use disorder). 75% of all inpatient discharges from the medical units with a behavioral health diagnosis had a SUD. Compared to 2020, the number of individuals with a primary diagnosis of SUD increased by 75% in the ED and 48% in the medical inpatient units in 2021. For the past three years, Native Americans comprised 56% of all admissions to the ED for alcohol use disorder. Furthermore, 30% of the ED behavioral health visits in 2021 were from designated rural communities of Sandoval County.

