### Eligibility criteria

Participants are adults 18 years of age or older who present to the ED or are admitted to a medical inpatient unit and who have screened positive for unhealthy use of alcohol, prescription medications (used nonmedically) and/or illicit drugs on the National Institute on Drug Abuse Tobacco, Alcohol, Prescription medication and other Substance Use (TAPS) (32). Individuals with unhealthy tobacco use only are excluded from the target population. Participants are excluded from the program if they are under 18 years of age, cannot speak English, are cognitively-impaired and therefore unable to provide consent, or do not wish to participate in treatment. Based on previous research with this population, the percent of non-English speaking individuals in our target population is less than one percent. Individuals who are not included in the study are still eligible to receive services through SRMC TH-SUD treatment and any other services at SRMC. The PSWs are responsible for conducting the screening and determining eligibility.

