### Outcomes

**Table 1** provides an overview of our primary, secondary and other outcomes, including the specific tool used to measure the outcome and measurement time point.

**Table 1 T1:** Overview of data collection.

Domain	Data Collection Tool	Time Point	Variable Type
Post-Traumatic Stress Disorder Symptom Severity	PTSD CheckList – Civilian Version (PCL-C) (44)	Baseline and every 60 days	Primary Outcome
Substance Use	Addiction Severity Index (45)	Baseline and every 60 days	Primary Outcome
Demographics	Age, race, ethnicity, gender (assigned at birth and current identity), relationship status, level of education, income level, employment status, health insurance status and provider, housing status	Baseline evaluation	Covariates
Criminal Activity Involvement	Criminal Justice Questionnaire (developed by first and second author)	Baseline and every 60 days	Secondary Outcome and Predictor
Motivation to Change	The Change Questionnaire (46)	Baseline and every 60 days	Secondary Outcome and Predictor
Treatment Satisfaction	Client Satisfaction Questionnaire (CSQ-8) (47)	Baseline and every 60 days	Secondary Outcome and Predictor
Quality of Life	36-Item Short Form Survey Instrument (SF-36) (48)	Baseline and every 60 days	Secondary Outcome and Covariate
Past Barriers to Substance Use Treatment	Barriers Questionnaire (49)	Baseline and every 60 days	Secondary Outcome and Covariate
Perception of Recovery	The Questionnaire about the Process of Recovery (QPR) (50)	Baseline and every 60 days	Secondary Outcome and Covariate
Self-Stigma	Substance Abuse Self-Stigma Scale (51)	Baseline and every 60 days	Secondary Outcome and Covariate
Substance Craving	3-Item Substance Craving Scale (52)	Baseline and every 60 days	Secondary Outcome and Covariate
Emergency Department Utilization	Services Use Questionnaire and EHR (developed by first and second author)	Baseline and every 60 days	Secondary Outcome and Covariate
Hospital and/or treatment facility utilization	Services Use Questionnaire and EHR (developed by first and second author)	Baseline and every 60 days	Secondary Outcome and Covariate

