### Participant interviews and consent

Once an individual agrees to engage in treatment, the PSW provides details about the opportunity to participate in a prospective follow-up cohort study. Individuals who are interested in participating sign a release of information agreeing to be contacted by a member of the research team. A member of the research team is then responsible for contacting individuals to provide further information about the study, obtaining consent for those who agree to participate and conducting baseline and follow-up interviews. Follow-up interviews are being conducted every 60-days post baseline. The consent process and all data collection is conducted by phone or a HIPAA compliant video conferencing platform. Individuals are compensated for their participation in the study with a $60 merchandise gift card for completing the baseline interview and $90 for every follow up assessment. The research team makes multiple attempts at varied times of the day and day of the week to consent individuals and complete baseline and follow up interviews. Participants are contacted via phone, text, mail and email. Participants are also offered a phone with monthly cell phone service to increase the likelihood of their participation in the study. Interviews range between 45 and 60 minutes. **Table 1** provides an overview of all data being collected during participant interviews, including the data collection tools and time point.

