To assess the impact of our covariates and secondary outcomes of interest, we will apply a multi-step approach to examine the significance of our independent variables. First, we will test for significant pre-post differences in our secondary outcomes to assess the impact of the variables from the start to finish of the client’s time in the program using parametric paired t-tests. Results of the paired tests will provide results to the significance of the impact pre-post on the client’s perceptions of the program and will provide validation of using the markers as covariates in the regression model. Second, we will apply two change-score multilevel regression models; one for the PTSD symptom severity outcome and one for the substance use outcome, with control variables (age, race, ethnicity, gender, relationship status, level of education, income level, employment status, health insurance status, provider and housing status), significant secondary outcome variables (quality of life, past barriers to substance use treatment, perception of recovery, self-stigma, substance craving, emergency department utilization and hospital treatment facility utilization) and predictor variables mentioned above. Examination of the multilevel regression model will allow for examination of client level deviation of the outcome variables by the time and predictor variables. *Post-hoc* analysis of the correlation matrix and pairwise t-tests of secondary outcomes and pre-post measurement will be examined to understand the impact of the markers in relation to the full scale of the data. Models will be used to assess for statistical robustness using the variance inflation factor for multicollinearity and appropriate error distribution tables. Latent-trait variables will be assessed for internal validity using exploratory factor analysis and reliability using Cronbach’s Alpha measure of internal consistency. While the primary outcome endpoint will be 120 days post-baseline, we will conduct secondary analyses to examine outcomes for participants using the last follow-up date post-baseline.

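### ED and hospital use is tested before versus after in people recruited through an ED visit or admission; unless that qualifying encounter is excluded, a significant fall in ED use is likely with no programme effect.

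*Protocol article*

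**What the plan says.** - **Design.** The Study design section describes a "Type 1 hybrid implementation design with a non-randomized approach". No comparison group is described.
- **Entry.** The Eligibility criteria section limits entry to "adults 18 years of age or older who present to the ED or are admitted to a medical inpatient unit", with a positive screen for unhealthy substance use also required.
- **Order of events.** The section headed Participant interviews and consent places cohort recruitment after agreement to treatment: "Once an individual agrees to engage in treatment, the PSW provides details about the opportunity to participate in a prospective follow-up cohort study". A signed release, contact by the research team, consent and the baseline interview come after that. Baseline therefore follows the hospital encounter.
- **Outcome.** Table 1 lists "Emergency Department Utilization" as a secondary outcome and covariate, taken from a services-use questionnaire and the EHR at baseline and every 60 days. Hospital and treatment-facility use share one further row with the same role, source and timing.
- **Test and its reading.** Under Effectiveness of the multi-level intervention: "First, we will test for significant pre-post differences in our secondary outcomes to assess the impact of the variables". The comparison runs from start to finish of the client's time in the programme and uses parametric paired t-tests.
- **Later use.** The same section treats these tests as validating the variables as covariates. It names ED use and hospital/facility use among the secondary outcomes that enter both primary-outcome models if significant.

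The article gives no look-back period for the utilisation counts and no rule for the qualifying encounter. It does not mention that people are selected on the quantity being measured.

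**The concern.** Recruitment requires an event of the kind that is later counted. A look-back from baseline will normally contain that event, while no follow-up window contains a guaranteed one. Without a comparison group, nothing separates the resulting drop from a programme effect.

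Two things are at stake. First, the section reads the pre-post difference as impact, so a drop created by how people entered could be taken as the programme reducing ED or acute hospital use. Second, significance in this test decides whether the utilisation variables enter the models for PTSD severity and substance use, so the way people were recruited can help set the covariates of the primary analyses.

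**Working it through.** The plan gives no figure on this point to reproduce. Its only calculated number, the sample size of 101, is used below as the number of pairs.

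**1. Background visit rate (Study site section).** The site reports that "1,366 patients, representing 1,958 visits, accessed the ED with a SUD diagnosis" in fiscal year 2021.
- Visits per patient: 1,958 / 1,366 = 1.43 per year. Everyone in this ratio has at least one visit, so it already contains a qualifying visit.
- Further visits after removing one per patient: (1,958 − 1,366) / 1,366 = 592 / 1,366 = 0.43 per year.

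**2. Expected change with no effect and equal windows of L days.** Let r be the yearly background rate.
- Baseline = 1 + r·L/365; follow-up = r·L/365.
- The absolute fall is exactly 1 visit per person, whatever r is.
- The proportional fall is 1 / (1 + r·L/365).

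| r per year | L = 60 days | L = 365 days |
|---|---|---|
| 0.43 | 1.07 to 0.07, fall 93% | 1.43 to 0.43, fall 70% |
| 1.43 | 1.24 to 0.24, fall 81% | 2.43 to 1.43, fall 41% |

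The 1.43 row counts a qualifying visit twice. It serves only as a high-background case.

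**3. How often the test would reject.** Null trials were simulated, 4,000 per setting. Each person had a Poisson visit rate with gamma variation between people, tilted towards frequent users because entry is through a visit. The true rate was the same before and after. Follow-up was 60 days and the baseline count was rescaled to 60 days. The test was a two-sided paired t-test at 0.05 with n = 101. Population rates ran from 0.5 to 3 per year and gamma shapes from 0.5 to 2.

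| Baseline look-back, qualifying visit counted for all | Mean change per 60 days | False significant fall |
|---|---|---|
| 60 days | −1.0 | about 100% |
| 180 days, rescaled | −0.33 (= 60/180) | 66–100% |
| 365 days, rescaled | −0.16 (= 60/365) | 26–97% |

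**4. If the qualifying event falls in the domain for only some participants** (60-day windows, 1.43 per year, shape 1, n = 101):

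| Share with the event | False significant fall |
|---|---|
| 10% | 16% |
| 25% | 66% |
| 50% | 99% |
| 75% | 100% |

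**5. With the qualifying visit excluded** (same settings):
- Stable rates: mean change about 0, and a significant fall in about 2.5% of trials, which is nominal for one tail.
- Pre-entry use assumed temporarily raised 1.5-fold or 2-fold: a significant fall in about 58% or 98%. This is regression to the mean, which exclusion does not remove.

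Step 5 also shows that the t-test is not the cause: on these skewed counts it keeps its nominal error once the guaranteed event is removed.

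**The case against.** The strongest reply is that the near-certain false fall needs the qualifying visit to be in the baseline count, and the article never says that it is. Look-back and index-visit handling are data-definition details that a condensed article may leave to a fuller document. Baseline also follows several steps with no stated maximum lag, so a short look-back could miss the visit.

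This stands as a limit on certainty but does not dispose of the point. The article itself fixes the test, its reading as impact and its downstream use, on an outcome that defines entry and without a comparator. The default result is misleading unless something further is specified. An unseen exclusion would also leave regression to the mean.

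A reader might infer more than the documents support:
- **That a fall is certain.** It depends on the look-back, the lag to baseline and the share with the event in each domain, none of which is stated.
- **That both measures will fall.** Entry is by ED or inpatient unit, and the second measure pools hospital with treatment-facility use, which may rise because the study supplies treatment. Its direction is undetermined.
- **That 81% is the expected size of the artefact.** It uses a background rate that already includes a qualifying visit, and that rate covers visits with a SUD diagnosis only, whereas Table 1 does not restrict ED use in that way.
- **That the t-test is at fault.** Any uncontrolled pre-post test would show the same drop.
- **That effectiveness will be claimed on utilisation.** The article assigns effectiveness to PTSD severity and substance use. The impact wording for secondary outcomes invites the misreading but does not state such a claim, and the effect on the primary models has not been quantified.

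**Conclusion.** The point holds in conditional form. Unless the qualifying encounter is excluded, a fall in ED use, and in acute hospital use among those admitted, is likely with no programme effect. It is near certain with a 60-day look-back that includes the encounter for everyone, and less so with long rescaled look-backs or when few participants have the event in that domain.

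These sizes rest on assumptions that are not in the article: 60-day follow-up windows, Poisson–gamma counts, rates stable over time, 101 complete pairs and no dropout. The pooled hospital/treatment-facility measure could move either way.

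The outcomes are secondary, so this should be corrected but does not overturn the design. It reaches the primary analyses only through the significance rule for covariates.

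**What to change.** - Exclude the qualifying encounter, and any admission linked to it, from the baseline count.
- Count ED and acute-hospital use from the EHR over equal windows, one ending before the qualifying encounter and one starting at discharge, and state their length.
- Report treatment-facility use separately from ED and acute-hospital use.
- Describe the change as uncontrolled, and state that regression to the mean remains after the exclusion.
- Do not use the significance of this test to select covariates for the primary-outcome models.

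A count model (negative binomial or Poisson mixed) is optional and does not by itself remove the bias.

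The cost is a revised EHR extract definition and a changed analysis paragraph. No new data collection is needed, since EHR extraction is already planned. The secondary result will probably look less favourable.

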### Sample size

We estimated our sample size using GPower (version 3.1.9.7) and focused on a meaningful change from baseline to six-months on the primary outcome PTSD symptom severity via a t-test means difference between two dependent means. The expected mean change in PTSD symptom severity as measured by the PCL-C was based on findings from research conducted by the first author in which PSWs implemented SS to a similar population (36). Assuming a moderate effect size, with an alpha = 0.05, and power = 0.80 the GPower analysis determined that a total sample size of 101 would be needed.

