The third challenge is the difficulty in engaging and retaining individuals in treatment. Challenges to substance use treatment engagement and retention are common (74, 75). In this particular study, while the participants have presented to the ED for injuries or illness related to the SUD (e.g., cirrhosis, pancreatitis), they may or may not make this connection and therefore may not be considering treatment for SUD. This could have a subsequent impact on their motivation for change, especially during the contacts that occur after their hospital encounter. It is also possible that within the initial meeting the PSWs do not have the opportunity to establish adequate rapport to assure that the relationship is of enough importance to ensure participant’s continued investment in further interactions. Examples of variables that may have impacted this are length of time the individual had been in the ED or inpatient unit, and the patient’s lack of alertness - due to intoxication and/or medications - during conversations with the PSW. This may account for some participants reportedly not remembering who the PSWs are when they are contacted post discharge and showing a reluctance to engage. Research on barriers to substance use treatment is extensive, with a recent overview of systematic reviews reporting 37 structural barriers (e.g., long waiting lists, expensive costs, insufficient options for treatment), 21 individual barriers (e.g., fear of stigma, motivational factors, psychiatric comorbidities), and 19 social barriers (e.g., difficulties with establishing a non-drug use network of friends, no supportive family) (76). There are barriers specific to our target population that are noteworthy. First, given that individuals are being recruited from the ED or medical inpatient, once discharged they are likely dealing with complex health and life circumstances that take priority over SUD treatment (77). Second, our intervention is based in a hospital that serves rural and tribal communities, and in both of these communities stigma, misinformation, mistrust and the lack of anonymity discourages individuals from seeking care (78, 79). Third, while providing services via telehealth could be perceived as being within the community, it may be that for certain participants, their preference may still be community-based providers and face-to-face interactions, versus this model of care. Finally, some of our patients from rural areas have had difficulty connecting to telehealth services because of not having broadband internet service; a challenge that has been reported in the literature on barriers to telemedicine in tribal communities (80). We have implemented several strategies to reduce barriers to care and hopefully decrease the low engagement and retention in treatment rates. First, when needed, we are providing individuals with cell phones and paid monthly cell phone plans so that they can access care provided via telehealth and to stay in contact with their PSW as well as research team. The phone comes preloaded with contact numbers for their PSW, the 988-crisis line, and Zoom and Teladoc apps to access telehealth appointments. The client has unlimited talk, text and data as long as they are engaging in services. If a client stops responding to calls and messages, they are given multiple reminders to re-engage and after six weeks of non-responsiveness, phone service is discontinued. Second, we are contacting patients multiple and various times throughout the day to schedule their appointments and are even willing to meet with patients after regular business hours if need be.

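### The paired tests of secondary outcomes take their end value at the finish of each client's time in the program, so the change they estimate belongs to no defined time

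*Protocol article*

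**What the plan says.** The statistical section gives three different time bases.

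- **Secondary outcomes.** The article states: "we will test for significant pre-post differences in our secondary outcomes to assess the impact of the variables from the start to finish". The full window and the test are given as "from the start to finish of the client’s time in the program using parametric paired t-tests". No day or visit is named.
- **Primary outcomes.** The time is fixed: "While the primary outcome endpoint will be 120 days post-baseline".
- **A further analysis.** The same sentence adds that "we will conduct secondary analyses to examine outcomes for participants using the last follow-up date post-baseline". This time differs by participant.

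Table 1 lists every secondary outcome at baseline and every 60 days. The section on participant interviews and consent agrees: "Follow-up interviews are being conducted every 60-days post baseline". Neither place states a last visit or an interview triggered by leaving the program.

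The paired tests also feed the main analysis. The article says their results will justify using these measures as covariates. It then lists seven secondary outcomes, described as the significant ones, among the terms of the two primary regression models.

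**The concern.** A paired t-test has no time term. It treats every end score as a measurement of the same thing at the same time. If that time is the point at which a client's program ends, it is set by treatment retention, which may itself be related to outcome. The resulting mean mixes change over time with differences between clients who stayed for different lengths of time. It could not be set beside the 120-day primary result, and another site with different retention could not reproduce it.

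The effect may reach the primary models. Whether a secondary outcome counts as significant, and so enters a 120-day model, could be decided by a test over a different and variable period.

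Variable time in the program is likely in this study. The Discussion reports: "The third challenge is the difficulty in engaging and retaining individuals in treatment".

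**Working it through.** The plan gives no figure of its own on this point, so there is none to reproduce. The sample size of 101 does not enter.

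**1. Does the finish of the program correspond to a scheduled measurement?**

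Inputs: interviews fall at day 60k, for k = 1, 2, 3 and so on (Table 1; participant interviews and consent). Clients choose Seeking Safety, pharmacotherapy or both, and the article states no common program length. Suppose a client's time in the program ends between day 60k and day 60(k+1). Two mappings to an interview are equally natural:

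| Program ends between | Last interview before the end | First interview after the end |
|---|---|---|
| day 0 and 60 (k = 0) | none after baseline, so no change score | day 60 |
| day 60 and 120 (k = 1) | day 60 | day 120 |
| day 120 and 180 (k = 2) | day 120 | day 180 |

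The article does not choose between them. Under either one, clients with different program durations contribute different times. No end score can precede day 60, so a client who leaves very early has either no change score or one from day 60 or later.

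**2. How far could the last-follow-up time range?**

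Inputs: 60-day interviews with no stated maximum, and the calendar limit in the section on the study site, "The study period is October 2022 – September 2024". Assume interviews continue to 30 September 2024 with full retention. Last scheduled visit = 60 × floor(days remaining / 60).

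| Baseline | Days remaining | Visits | Last visit |
|---|---|---|---|
| 1 Oct 2022 | 730 | 12 | day 720 |
| 1 Apr 2023 | 548 | 9 | day 540 |
| 1 Oct 2023 | 365 | 6 | day 360 |
| 1 Apr 2024 | 182 | 3 | day 180 |
| 1 Jun 2024 | 121 | 2 | day 120 |
| 1 Aug 2024 | 60 | 1 | day 60 |

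Enrolment date alone therefore gives 60 to 720 days, and 720/60 = 12. This is a ceiling. If follow-up stopped at the six months used in the sample size section, the range would be 60 to 180 days, and 180/60 = 3.

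**3. What could a variable last visit do to the mean change?**

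This simulation is for the last-follow-up analysis and rests on assumptions, because the article gives no retention rate or trajectory. Enrolment is uniform over the first 670 days (730 − 60). Everyone has at least one follow-up. Retention from one interview to the next is 0.9, 0.75 or 0.6. Last visit = the smaller of the retention-limited visit and the calendar-limited visit. Mean change is expressed as a multiple of the day-120 change.

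| | Retention 0.9 | 0.75 | 0.6 |
|---|---|---|---|
| Last visit is day 120 | 15% | 22% | 25% |
| 5th–95th percentile of last visit (days) | 60–600 | 60–420 | 60–300 |
| Change linear in time | 2.22 | 1.48 | 1.08 |
| Change levels off at day 120 | 0.91 | 0.84 | 0.77 |
| Change returns to zero by day 360 | 0.42 | 0.57 | 0.63 |

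Under these assumptions the same day-120 effect appears as anything from about 0.4 to 2.2 times its size.

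**The case against.** The strongest defence is that the finish-of-program wording is descriptive prose. The article uses the same pre-post language for the primary outcomes, where the end time is 120 days, and the paired tests are the first step towards the primary models. On that reading 120 days applies throughout, and a condensed article may leave the visit label to a fuller document. This may be what the authors intend. But the text names 120 days only for the primary outcomes and gives the secondary tests a different window in words. That is a stated rule that conflicts with the interview schedule, and more than an omitted detail.

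It can also be said that the multilevel models examine change by time. They do so for the two primary outcomes; the secondary outcomes get paired t-tests.

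On the last-follow-up analysis the defence is largely right. It is already labelled secondary, stands beside a fixed primary endpoint and keeps everyone with any follow-up. Replacing it with a fixed later visit such as day 180 would exclude people lost earlier or enrolled too late, so replacement is not clearly better.

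Three stronger readings are tempting but unsupported:

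- *Early end scores come mainly from people who disengaged.* Interviews are done by the research team, by phone or video, with compensation and repeated contact attempts. Nothing says they stop when treatment stops. The reported difficulty concerns treatment retention, no interview retention is given, and late enrolment also produces early last visits.
- *The timing really varies 12-fold.* That needs a baseline at the very start of the period and interviews to its end. The article states neither an enrolment start date nor a maximum number of interviews. The only longer horizon named with an outcome is in the sample size section, which "focused on a meaningful change from baseline to six-months on the primary outcome PTSD symptom severity".
- *No usable time is fixed anywhere.* The 120-day endpoint stands in the same sentence as the last-follow-up analysis.

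**Conclusion.** The point holds for the paired tests of the secondary outcomes. As worded, their end time varies by client with time in treatment and matches no scheduled interview, so the mean change has no defined time. It may also not match the 120-day primary models, and that matters because these tests help decide which of seven secondary outcomes enter those models.

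The size cannot be stated from the documents, which give neither program durations nor retention rates. The 60-to-720-day range and the 0.4-to-2.2 multiples concern the last-follow-up analysis only. The first is a theoretical limit and the second depends on assumed enrolment, retention and trajectories. They show that the choice of end time can matter, not what this study will find.

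A reader might infer that the primary endpoint has no fixed time either. It does not follow: 120 days is stated for it. For the last-follow-up analysis, the remaining point is one of labelling and reporting.

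**What to change.** **Secondary outcomes.** State that the end value for every secondary outcome is the 120-day interview, for all participants regardless of whether they are still in treatment, and remove the reference to the finish of the client's time in the program. The tests then share a time base with the primary models they feed.

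**Last-follow-up analysis.** Keep it as secondary, label it descriptive, and report it by time since baseline or include that time in the model, because its timing depends on interview retention and enrolment date.

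**Cost.** This is a change of wording; the 60-day interviews already supply the data. Interviews after day 120 drop out of the paired comparison. People without a day-120 interview will be missing from it, including anyone with a baseline after 2 June 2024 (120 days before 30 September 2024) if interviews stop when the study period ends. The primary outcomes share that limit. A fixed visit defines what is estimated; it does not solve missing data.
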